#### Treatment adherence

To assess treatment adherence, the trainer indicates after a series of three lessons which strategies were used, level of treatment adherence, and whether the lessons were completed. Furthermore, a subsample of lessons will be observed by an expert in R&W to assess treatment adherence, quality of delivery, participants’ engagement, and adaptations. This coding schema is based on Bishop and colleagues [58]. Treatment adherence indicates the level to which the trainer has conducted the lesson as described in the manual (e.g., “Skipped the trainer exercises?”). Quality of delivery is an indication of the general quality of the lesson (e.g., “Are the goals of the lesson met?”). Participants’ engagement indicates the level to which the trainer actively involves the students in the lessons and the extent to which the trainer can activate students physically (i.e., exercises) and mentally (i.e., reflection; e.g., “Do students respond to questions of the trainer?”). Adaptations are clear deviations from the manual. These can be adaptations to the exercises, structure of the exercise, instructions and adding steps to an exercise (e.g., “What percentage of the exercises of the lesson are adapted?”).

#### Statistical analyses

The power calculations are based on the N:q rule for structural equation models [59]. This rule states that for each free parameter (q) 10 to 20 participants (N) are needed. We took the conservative approach by taking 20 participants per free parameter for our power calculations. In our multigroup LGC model there are 9 free parameters per condition, 36 free parameters in total. Thus a total sample of 720 participants is needed for our analysis, 180 participants in each condition. Since not only students can drop out but also classes (about 20 students) and schools (about 60 to 90 students), we will include three to four schools per condition. Missing data will be handled in M*plus*.

In our data, students are nested in classes which are nested in schools. Therefore, we will examine whether there is significant intra-class correlation on one of the levels (i.e., school, and class) and we will calculate the design effect. Each level with a design effect larger than 2.0 will be modeled in the analyses which allows us to correct for the nested data, that is multilevel analyses [60].

The first aim is to examine the effectiveness of R&W in the conditions which differ in the number of parties involved in the intervention. This will be examined using an analysis of covariance (ANCOVA) for the outcomes of socio-emotional adjustment and social safety, in case the design effect is smaller than 2.0. The dependent variables will be the post-measurements after the second year (8th Grade), the independent variables the condition, and the covariates the premeasurements (7th Grade). If needed, due to large design effects, multilevel regression analyses will be used (This also holds for the other aims). Then, we will analyze the trajectories of change in socio-emotional adjustment and social safety during R&W with multigroup Latent Growth Curve (LGC) modeling in M*plus*. We will examine if these trajectories of change differ significantly between the four conditions.

The second aim, the effect of potential moderators on the effectiveness of R&W on socio-emotional adjustment and social safety, will be examined using ANCOVAs for categorical moderators and regression analyses for the continuous moderators. The interaction effects of the concerned outcome measure with the student, trainer or parent characteristics will be added as an interaction term.

The third aim, studying the working mechanisms of R&W, will be examined by analyzing multiple mediators. We will analyze whether the R&W intervention improves students’ self-control, self-reflection, self-esteem and emotion regulation by performing ANCOVAs. Furthermore, we will analyze whether the change in these concepts mediate the relation between R&W and socio-emotional adjustment and social safety through LGC modeling in M*plus*. We will model the mediators as well as the outcome measures in this mediation analysis on the assessments before, during, and after R&W [61]. Furthermore, we will study whether R&W decreases deviant communication and increases prosocial communication. We will analyze if changes in deviant and prosocial communication are mediators of the effect of R&W on social safety. We will model these indirect effects in M*plus* using bootstrapping.

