**Fig. 1 Fig1:**
[figure not shown]
Flow chart

Students receive R&W for two years. The intervention is implemented during physical education classes by (mostly) physical education teachers who followed the three-day training. After successfully terminating this training, these teachers are certified R&W trainers. Socio-emotional adjustment (i.e., psychosocial wellbeing, sexual autonomy, and resilience), social safety (i.e., perceived social security in the classroom, aggression, and bullying), and mediators (i.e., self-control, self-reflection, self-esteem, and emotion regulation) will be assessed at multiple measurement points: Prior, during and after R&W in the first and second year and at follow-up. These concepts are assessed with online questionnaires completed by students, parents, and teachers. The interim measurements (during R&W) are shortened questionnaires and are completed by students after a series of three R&W lessons. Deviant and prosocial communication is assessed in the first year prior and after R&W using video-observations in a subsample. Moderators (i.e., student, teacher, and parent characteristics) are assessed at one time point.

The study is registered with the Dutch Trial Registration (6554) and has been approved by the Ethical Committee of the Faculty of Social and Behavioral Sciences of Utrecht University (FETC17–015).

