### Study sample

In total, we aim to include 720 students in this study across all waves, 180 per condition. Participants are students in the 7th Grade, in the second year of the intervention in the 8th Grade, of preparatory vocational education level. Schools are excluded if they currently implement R&W in the whole school or have implemented the intervention in the past two years in the whole school. Additionally, schools for students with special needs are excluded from the study.

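### The 720-student figure is called a conservative power calculation, but it ignores school randomisation and gives no power for the comparison between conditions

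*Protocol article*

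**What the plan says.** The Statistical analyses section of the protocol article bases the sample size on the N:q rule for structural equation models: "This rule states that for each free parameter (q) 10 to 20 participants (N) are needed". It continues: "We took the conservative approach by taking 20 participants per free parameter for our power calculations". The count is given as "In our multigroup LGC model there are 9 free parameters per condition, 36 free parameters in total", and the conclusion is "Thus a total sample of 720 participants is needed for our analysis, 180 participants in each condition". Study sample repeats the target: "In total, we aim to include 720 students in this study across all waves, 180 per condition".

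Three other statements bear on this figure:

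- Recruitment says that whole schools are randomised, 1:1:1:1, in blocks of four stratified by school size.
- Statistical analyses says that students are nested in classes and classes in schools. A level is modelled only if its design effect exceeds 2.0. This check is made on the collected data and does not feed into the 720.
- For dropout of students, classes (about 20 students) and schools (about 60 to 90 students), the same section says "we will include three to four schools per condition".

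The section states no alpha, power, effect size or ICC.

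**The concern.** The section makes two claims for the 720: that it is a power calculation and that it is conservative. A ratio of students to parameters is a rule of thumb for fitting a structural equation model. It gives no probability of detecting a difference. The first analysis of aim 1 is an ANCOVA, or a multilevel regression, of the year-2 post-measurement by condition. Its precision depends mainly on the number of schools per arm and the between-school variance, and neither enters the calculation.

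A raw student count that leaves out the unit of randomisation also errs in the unfavourable direction, so it cannot be called conservative. What is at stake is how the results are read. Without a stated detectable difference, nobody can judge whether a non-significant contrast, including one between the Light, Standard and Plus conditions, excludes an effect worth having.

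**Working it through.** **1. The plan's own figure.** 9 parameters × 4 conditions × 20 students = 720, and 720 / 4 = 180 per condition. This reproduces.

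**2. Students per parameter after clustering.** School size m is about 60 to 90 (Statistical analyses). The ICC is assumed. Design effect DE = 1 + (m − 1) × ICC, and effective ratio = 20 / DE.

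| ICC (assumed) | DE, m = 60 to 90 | Effective students per parameter at N = 720 |
|---|---|---|
| 0.01 | 1.59–1.89 | 12.6–10.6 |
| 0.02 | 2.18–2.78 | 9.2–7.2 |
| 0.05 | 3.95–5.45 | 5.1–3.7 |

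At the plan's own limit, DE = 2.0, 720 students act as 360, and 360 / 36 = 10, the bottom of the quoted 10–20 range. DE reaches 2.0 when ICC = 1 / (m − 1), that is 1/59 = 0.017 for schools of 60 and 1/89 = 0.011 for schools of 90.

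**3. Detectable difference, one intervention arm against control.** Assumptions: two-sided alpha 0.05, 80% power, baseline correlation r = 0.6 acting equally at school and student level, no separate class effect, and k schools per arm with 4(k − 1) degrees of freedom. The variance of the difference in SD units is (1 − r²) × (ICC + (1 − ICC)/m) × 2/k. The required non-centrality (non-central t) is 3.20 for 8 df and 3.05 for 12 df.

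Worked case, k = 3, m = 60, ICC 0.01: 0.64 × (0.01 + 0.99/60) × 2/3 = 0.0113; the square root is 0.106; × 3.20 = 0.34 SD.

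| Schools × students per arm | ICC 0.01 | ICC 0.02 | ICC 0.05 |
|---|---|---|---|
| 3 × 60 = 180 | 0.34 | 0.40 | 0.54 |
| 3 × 90 = 270 | 0.30 | 0.37 | 0.51 |
| 4 × 60 = 240 | 0.28 | 0.33 | 0.44 |
| 4 × 90 = 360 | 0.25 | 0.30 | 0.42 |

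For 180 independent students per arm: 2.80 × √(0.64 × 2/180) = 0.24 SD. So at ICC 0.01 even 360 clustered students per arm only about match 180 independent ones.

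All these values scale with √(1 − r²), which is 0.8 here. With no gain from the baseline (r = 0), divide by 0.8: 0.43/0.50/0.67 for 3 × 60, 0.31/0.38/0.53 for 4 × 90, and 0.30 under independence.

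**4. Reserve for dropout.** Planned recruitment is 3 × 60 = 180 to 4 × 90 = 360 per condition. At 3 × 60, one lost class leaves 160 and one lost school leaves 120. At 3 × 90 or 4 × 60, one lost school leaves 180. At 4 × 90 it leaves 270.

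**5. Parameter count (conditional).** The nine parameters are not itemised. If the model is a linear growth curve with free residual variances (an assumption), there are 2 means + 2 variances + 1 covariance + T residual variances = 5 + T per condition, so nine corresponds to T = 4 waves. The Design section describes measurement as "Prior, during and after R&W in the first and second year and at follow-up", which is at least 3 + 3 + 1 = 7 waves. On seven waves the same model has 12 × 4 = 48 parameters, and 720 / 48 = 15 students per parameter.

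**The case against.** The strongest reply has four parts.

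- **N:q is a raw-count rule as the article quotes it.** Dividing by a design effect is an extension, and at DE = 2.0 the result of 10 is still inside the quoted range. Levels above 2.0 are to be modelled. This stands as a caution on the ratios in step 2, which are therefore labelled an effective-sample reading. It does not rescue the word conservative, and it does not touch the missing power for aim 1. Modelling a level protects the standard errors but does not restore the lost information.
- **The plan over-recruits.** At 4 × 90 per condition, 1,440 students over 36 parameters with DE 1.89 give 21.2 per parameter at ICC 0.01, above 20. This stands. A reader might infer that dropout takes every version of the design below 20 per parameter, but the shortfall arises only toward the low end of recruitment. The school sizes are also approximate.
- **The wave count is unknown.** The model may use four waves or constrain the residual variances. With equal residuals a linear curve has 6 parameters whatever the number of waves. The growth model is described as covering change during the programme, and the measurement table is in an additional file not shown here. A reader might infer that the parameter count is wrong. The article does not support that, and 15 per parameter would still lie within 10–20.
- **The detectable differences rest on an ICC and a baseline correlation that the article does not give.** This is true, so the full range is shown. It is tempting to say that the trial can detect only medium-to-large effects. With r = 0.6 the values run from 0.25 to 0.54 SD, which does not bear that out.

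**Conclusion.** The concern holds for the basis and labelling of the 720, not for its arithmetic. The figure treats students as independent in a school-randomised trial and gives no power for the between-condition comparison, so neither label is supported.

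At a fixed 720, any positive ICC takes the effective ratio below 20. An ICC of 0.011 to 0.017 is enough to halve it. The detectable difference exceeds the 0.24 SD of 180 independent students per arm in every configuration shown, marginally at 4 × 90 with ICC 0.01 and by more than a factor of two at 3 × 60 with ICC 0.05. The direction does not depend on the assumed values. The size depends on the ICC, the baseline correlation and the number of schools.

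The lack of reserve at the 3 × 60 end is a lesser point. The mismatch between nine parameters and the planned waves is a question for the authors, not an established error.

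**What to change.** Rewrite the sample-size paragraph of Statistical analyses:

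1. Present 20 × 36 = 720 as a rule of thumb for fitting the growth model, and remove the power and conservative labels from it.
2. State the minimum detectable difference for the school-randomised contrast, with alpha, power and the assumed baseline correlation, over a stated ICC range, for 12 and 16 schools in total and 60 to 90 students per school.
3. Restate the students-per-parameter ratio after the design effect.
4. Say that recruitment of 3 × 60 = 180 per condition leaves no reserve for a lost class or school, and that one lost school leaves 180 at 3 × 90 or 4 × 60.
5. Itemise the nine parameters and name the waves that enter the growth model, so that the two can be reconciled.

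The cost is one paragraph. No extra enrolment is needed. The published figures become less favourable.

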Previous intervention research has shown that personality can be a moderator of intervention effectiveness. Senf and Liau [16] have found the strongest intervention effects on happiness for individuals with high levels of extraversion and openness and on depressive symptoms for individuals with high levels of extraversion. Asscher and colleagues [17] have shown that Multisystemic Therapy was less effective than treatment as usual in decreasing rule-breaking behavior for adolescent with low levels of agreeableness. Stoltz and colleagues [18] have found the strongest intervention effects on reactive aggression for children with a low level of extraversion and on proactive aggression for children with less extreme levels of conscientiousness. Hence, it is expected that personality also influences the effectiveness of R&W. It is hypothesized that R&W is most effective for students with higher levels of agreeableness and openness, and average levels of conscientiousness. No specific hypothesis concerning extraversion is stated, since the results [16, 18] are inconsistent.

Besides the student characteristics, we will also study trainer characteristics: Gender, ethnicity, education level, level of self-perceived competence, expertise, and degree of training and supervision. Findings concerning characteristics of professional therapists are inconsistent. Whereas some studies have found significant impact of (one of) these characteristics on treatment outcome [19–21], other studies have found no relation [22, 23]. Characteristics of (non-professional) therapists are often neglected in intervention studies. By studying trainer characteristics of non-professional therapists as moderators we will clarify the role of these characteristics on the effectiveness of R&W. We hypothesize that R&W is more effective when trainers are males, have a Western ethnic background, have a higher education level, have more self-perceived competence, have more expertise, and received more training and supervision.

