## Methods

### Design

To study the effects of R&W an RCT design is implemented in the 7th Grade of preparatory vocational education level. Schools from different parts of The Netherlands are randomly assigned to one of three intervention groups or to the control group (Fig. 1). In the ‘Light’ condition a core team of teachers is trained with the three-day training course to become certified R&W trainers and implement the R&W program. In the ‘Standard’ condition a core team is trained to become R&W trainers and the rest of the school-team that teaches 7th Grade students follows a three-day training to learn how they can support the R&W trainers of their school and how they can apply R&W in their regular classes. The ‘Plus’ condition is equal to the ‘Standard’ condition with the addition of a parent component. The parents watch a documentary of R&W, get an invitation to join a lesson in the school, receive weekly e-mails with information about the lesson of that week and are stimulated to act on this information, for instance by communicating about R&W or using R&W language. This will not only create a supporting environment within the school, but also in students’ homes. In the control condition students receive CAU; i.e., current school policy to enhance socio-emotional adjustment and social safety of students.

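### The trainer-characteristic tests have no trainer level: where trainers teach several classes and share a school, the class and school levels do not supply the right error term

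*Protocol article*

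**What the plan says.** The Background section announces the analysis: "we will also study trainer characteristics: Gender, ethnicity, education level, level of self-perceived competence, expertise, and degree of training and supervision". It attaches directional hypotheses to these characteristics: "We hypothesize that R&W is more effective when trainers are males, have a Western ethnic background, have a higher education level", and likewise for self-perceived competence, expertise, and training and supervision.

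The Statistical analyses section says that moderators "will be examined using ANCOVAs for categorical moderators and regression analyses for the continuous moderators", and trainer characteristics are among those entered as interaction terms.

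On clustering, the same section says that "students are nested in classes which are nested in schools". It will look for "significant intra-class correlation on one of the levels (i.e., school, and class", which reads as a closed list. The rule is then: "Each level with a design effect larger than 2.0 will be modeled in the analyses". For the moderator aim, the fallback is that "multilevel regression analyses will be used (This also holds for the other aims". It therefore brings in class and school and nothing else.

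On delivery, the Design section says that "a core team of teachers is trained with the three-day training course to become certified R&W trainers", and the description of the R&W program has lessons given to whole classes. The article does not state how many trainers a school has or how many classes each trainer takes.

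**The concern.** A trainer's gender, education or expertise takes one value for all the students that trainer teaches. Those students also share whatever that trainer does well or badly for unrelated reasons. The evidence on whether a characteristic matters therefore comes from comparing trainers, and the standard error has to reflect variation between trainers.

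A trainer with several classes, in a school with other trainers, sits between class and school. Neither listed level then replaces the missing one:

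- With no level modelled, students count as independent evidence.
- With school modelled, two trainers in the same school are compared against student-level noise.
- With class added, two classes of the same trainer still count as independent given the school.

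The problem remains when the analysis is restricted to the three R&W conditions, so it is separate from control schools having no R&W trainers. At stake are false-positive findings on six hypothesised moderators. The main comparison of conditions is not affected.

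**Working it through.** **The plan's own figure.** The N:q rule gives 20 participants × 9 parameters × 4 conditions = 720, or 180 per condition. This reproduces the stated sample size. It says nothing about trainer moderators, and the article gives no power, effect size or ICC for them.

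**Inputs from the Statistical analyses section.** Classes have about 20 students and schools about 60 to 90, with three to four schools per condition. That gives 9 to 12 R&W schools and 27 classes (9 × 60 / 20) to 54 classes (12 × 90 / 20). If a core team means at least two people, there are at least 18 to 24 trainers. One trainer per class would give 27 to 54.

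**Assumptions.** Trainer ICC is 0.02 to 0.05, with no further class or school variance. The base layout is two trainers per school with two classes of 20 each (40 students per trainer, 80 per school).

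**Formula check, no level modelled.** Design effect DE = 1 + (m − 1) × ICC. The true error of a nominal 5% test that ignores it is 2 × [1 − Φ(1.96/√DE)]. With m = 40:

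- ICC 0.02: DE = 1 + 39 × 0.02 = 1.78, error 14%.
- ICC 0.05: DE = 1 + 39 × 0.05 = 2.95, error 25%.

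**Simulation.** A binary trainer characteristic with no true effect, 400 runs per row, Monte Carlo error about 1 to 2 points:

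| R&W schools | Trainers × classes per school | Trainer ICC | No level | School | Class + school | Trainer means |
|---|---|---|---|---|---|---|
| 9 | 2 × 2 | 0.02 | 16.8% | 14.2% | 12.2% | 6.2% |
| 9 | 2 × 2 | 0.05 | 26.0% | 22.8% | 14.0% | 5.8% |
| 12 | 2 × 2 | 0.02 | 14.2% | 11.8% | 8.8% | 4.5% |
| 12 | 2 × 2 | 0.05 | 21.8% | 18.8% | 12.2% | 4.5% |
| 9 | 4 × 1 | 0.02 | 9.2% | 10.0% | 5.5% | 5.0% |
| 9 | 4 × 1 | 0.05 | 13.5% | 13.5% | 6.2% | 5.5% |
| 9 | 1 × 4 | 0.02 | 23.8% | 10.8% | 10.8% | 6.2% |
| 9 | 1 × 4 | 0.05 | 38.2% | 7.2% | 7.2% | 4.0% |

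The two mixed-model columns use a normal reference distribution, which adds some inflation of its own with few schools. A separate simulation of the 2 × 2 layout with 4,000 runs gave 14.7 to 25.7% at student level, 8.5 to 11.7% for a class-level test and 4.6 to 5.3% on trainer means.

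**Which column the plan would use.** A level is modelled when DE exceeds 2.0, that is when ICC > 1/(m − 1):

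- Class of 20: 1/19 = 0.053.
- School of 60 to 90: 1/59 = 0.017 to 1/89 = 0.011.

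In the 2 × 2 layout, trainer variance also shows up as school clustering. The expected school DE is 1 + 79 × (39/79) × ICC = 1.78, 2.17 and 2.95 at ICC 0.02, 0.03 and 0.05. The class DE is 1 + 19 × 0.02 = 1.38 and 1 + 19 × 0.05 = 1.95 at ICC 0.02 and 0.05. In expectation, then, no level is modelled at 0.02 and only school at 0.05. Class is added only if classes differ for further reasons.

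**The case against.** The strongest reply is that the deciding facts are not in the article. A school of 60 to 90 students has roughly three to four and a half classes, so a core team of three or four could take one class each, and class would then be the trainer level. With one trainer per school, school would be. This stands, and it makes the point conditional. It does not remove the need to settle the matter. With one class per trainer, class has to be modelled to help, and at ICC 0.05 its design effect of 1.95 falls short of the cut-off.

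A second reply is that the student-level rates overstate what the plan would do, because the school level is triggered at a low ICC. This also stands in part. At trainer ICC 0.03 to 0.05 school would be modelled in about half to three quarters of runs, so 25% is not a fair single figure for the plan. The rates with school modelled (12 to 23%) and with both levels modelled (9 to 14%) still exceed 5%.

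A third reply is that a random effect for one set of moderators is detail for an analysis plan. Silence would have been no finding, but the article sets out the levels as a closed list and states the rule for using them.

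Two stronger readings are not supported. A reader might infer that the tests rest on a very small number of trainers. The article gives no number, and a team of at least two in each of 9 to 12 schools means at least 18 to 24. A reader might also infer that the results will steer which teachers become trainers. The Background section aims only to clarify the role of these characteristics. The Abstract and Discussion speak of levels of school and parental involvement and of student subgroups.

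**Conclusion.** The point holds conditionally. Where a school has two or more trainers and a trainer takes two or more classes, no combination of the listed levels gives a trainer-level error term. In the assumed 2 × 2 layout the false-positive rate is about 14 to 25% with no level modelled and stays above 5% under every combination of levels that the plan can reach, against about 5% on trainer means. With one class per trainer and class modelled it is about 6%. With one trainer per school and school modelled it is 7 to 11%, where the normal reference distribution with nine schools contributes.

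The ICCs, the trainers per school and the absence of other clustering are assumptions. Real class or school variance would make the plan's own levels more likely to be modelled. The finding is confined to the trainer moderators within the second aim.

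**What to change.** In Statistical analyses, state for the trainer-characteristic analyses:

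- They are run within the R&W conditions with a trainer random effect, included whatever its design effect.
- Degrees of freedom are small-sample and based on the number of trainers.
- School enters as a random effect and condition as a fixed effect. Both cannot be fixed, because schools are randomised to condition and school therefore determines condition.
- Alternatively, trainer means are analysed, adjusted for pre-score and condition. The simulation had no school variance, so where schools differ the school random effect is needed here too.
- The number of trainers, overall and in each category of a characteristic, is reported as the sample size for these tests, together with the number of classes per trainer.

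The change needs a trainer identifier linked to each class and some analysis work, but no further participants or measurements. The price is wider intervals for the trainer moderators, which reflects the information that the design holds on them.
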